### Postoperative muscle spasm assessment

3.7

This result is usually evaluated by measuring the distance between the incisal edges of the upper and lower central incisors, using a caliper rule. In the present study, the evaluator will measure the opening of the mouth in each patient 1, 2, 5 and 7 days after surgery.

### Temperature

3.8

The temperature will be measured locally and systemically in each patient 1, 2, 5, and 7 days after surgery. The local measurement will be done with a digital thermometer (Safety 1st, “No Touch Forehead”, Columbus), in the region of the mandibular angle, 2 cm above the lower border of the mandible and 3 cm for mesial of the branch of the mandible, both on the operated side and on the opposite side. The systemic temperature will be measured in the frontal region of the patient in the median position 3 cm above the glabella in the same time frames.

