**Methods::**

A randomized, double-blind, placebo-controlled clinical trial involving 38 adult participants, who meet the criteria of eligibility and agree to participate in the study. Before the surgeries are performed, the facial and mouth opening measures of all the participants will be taken. Immediately after the surgeries, participants will be randomized into 2 groups. In the LED group, participants will receive LED applications (intra oral with 660 nm, 12J and extraoral with 850 nm, 108J) in the immediate postoperative, first and second days after the surgical procedure. In the control group, the participants will be attended in the same way as in the LED group, however, the person in charge of the application will simulate the irradiation. Pain (EVA and NRS-101), postoperative edema, trismus, temperature, dysphagia, and hematoma will be evaluated after 1, 2, 5, and 7 days. The oral health impact profile (OHIP-14 Questionnaire) and anxiety analysis (Beck anxiety inventory -BAI) questionnaires will be applied preoperatively and 7 days after treatment. The appropriate statistical tests will be applied for each specific analysis in a significance level of 5%.

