### Sample calculation

2.3

A sample calculation based on the parameters of variability of the article of Eshghpour, Ahrari ^[13]^ based on the pain analysis of the participants on the 3rd postoperative day evaluated by a visual analog scale (VAS) was performed. Using a power of 80% and level of significance of 5%, a minimum sample size of 17 cases per group was obtained, making a total of 34 participants for the study. Winpepi software version 10.5 was used for this calculation. Considering a loss of 10%, based on the study that was used for the sample calculation, a loss of 2 participants per group should be predicted. Therefore, the total number of participants to be selected will be 38 individuals.

*Inclusion criteria*:Need of surgical removal of retained lower third molars;Agree to participate in the study after reading and signing the Informed Consent Term;Participants with indication for extraction of lower third molars (recurrent infections, bad position, and orthodontic indication) or professional written indication, healthy patients (negative medical history), systolic blood pressure lower than 140 mm Hg, and diastolic blood pressure lower than 90 mm Hg and heart rate values of 70 ± 20 beats/minute. The upper and lower central incisor teeth must be present.

*Exclusion criteria*:Systemic diseases, chronic pain or neurological and psychiatric disorders;Smokers;Using anti-inflammatories, analgesics or bisphosphonates in the last 15 days;Present active pericoronarite;Pregnant;Breastfeeding;Severe temporomandibular disorders;Photosensitivity history;Allergic to any drug used in the research (paracetamol, chlorhexidine 2%);Participants presenting radiolucent images associated with the teeth to be extracted;Participants who present any type of complication during surgery (hemorrhage, operative difficulty, time greater than 90 minutes of surgery), as these cases are not in the standard expected for third molar surgeries. In this case, the central action analgesic will be prescribed. These data will not be part of the statistical analysis but will be described and discussed.

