#### Facial measures

3.1.1

Measurements of the distances between the corner of the eye and the angle of the mandible, between the tragus and the labial commissure, and between the tragus and the pogonium of each patient will be taken before the surgical procedure.

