### Postoperative pain evaluation

3.5

In this project, we intend to apply 2 scales: the VAS and NRS-101. The VAS will be printed on the patient evaluation form and the subjects will be instructed by the evaluator to mark a point on the 10 cm line, indicating the intensity of their pain after 1.2, 5, and 7 days of the surgeries For the NRS-101 scale, the evaluators will ask participants to assign a number between 0 (no pain) and 100 (worst possible pain) that best represents the pain they are currently experiencing after 1, 2, 5, and 7 days of surgeries.

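### Temperature and pain are efficacy outcomes with no preoperative reading in the text; the arm comparison stays unbiased, but precision and any check on chance baseline imbalance are lost, chiefly for systemic temperature

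*Protocol article*

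**What the plan says.** The introduction of the protocol article lists pain control and temperature among the outcomes on which efficacy will be judged.

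- **Temperature (section 3.8):** "The temperature will be measured locally and systemically in each patient 1, 2, 5, and 7 days after surgery". Local readings are taken "both on the operated side and on the opposite side". The systemic reading is a forehead reading at the same times.
- **Pain (section 3.5):** the VAS is marked "indicating the intensity of their pain after 1.2, 5, and 7 days of the surgeries", and for NRS-101 the participant gives the number "that best represents the pain they are currently experiencing after 1, 2, 5, and 7 days of surgeries".
- **Preoperative assessment (section 3.1 and the abstract):** the abstract says "Before the surgeries are performed, the facial and mouth opening measures of all the participants will be taken". Section 3.1 has these two items and no other.
- **Questionnaires (sections 3.11 and 3.12):** OHIP-14 and BAI are given before surgery and on day 7, each stated in its own section.
- **Eligibility (section 2.3):** accepted indications include "recurrent infections, bad position, and orthodontic indication". Chronic pain, active pericoronitis, and analgesic or anti-inflammatory use in the preceding 15 days are excluded.

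Participants are randomised immediately after surgery, and the first LED or sham session follows at once. The day 1 reading therefore comes after surgery and at least one session.

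**The concern.** The measurement schedule is fixed in the protocol, and no later analysis plan can restore a reading that was never taken. Without a preoperative value, individual change cannot be described for systemic temperature or pain. A chance difference between the arms in starting level can be neither seen nor adjusted for, and the precision that a baseline covariate brings is given up. Section 2.4 describes a simple draw of numbers without stratification, so nothing in the allocation offsets such a difference. With 19 per arm the precision matters, and the missing readings would need only equipment and scales already in use.

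**Working it through.** **1. Is the reading absent?** The sentence in section 3.8 does not settle this alone. Edema (3.6) and mouth opening (3.7) are scheduled on the same days, and both have a preoperative value because section 3.1 provides it. The test is whether a preoperative time appears anywhere in the text:

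| Outcome | Preoperative time in the text |
|---|---|
| Facial distances | Yes (3.1.1, abstract) |
| Mouth opening | Yes (3.1.2, abstract) |
| OHIP-14 | Yes (3.11, abstract) |
| BAI | Yes (3.12, abstract) |
| Local temperature | None; opposite side read at each postoperative visit (3.8) |
| Systemic temperature | None (3.8) |
| VAS, NRS-101 | None (3.5) |

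Section 3.4 mentions preoperative evaluations without listing them. Figure 1, the SPIRIT schedule, is not shown. Absence is therefore established for the readable text only.

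**2. The plan's own sample size.** From 17 per group and 10% loss: 17 / (1 − 0.10) = 18.9, rounded up to 19 per group, 38 in total. This agrees with section 2.3. The step to 17 cannot be reproduced because no difference or SD is given. Worked backwards (two-sided 5%, 80% power, normal approximation), the standardised difference is √(2/17) × (1.96 + 0.84) ≈ 0.96. That two-sided value is an assumption, used only for illustration in step 5.

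**3. Chance imbalance in starting values, 19 per arm.**
- Standard error of the difference in baseline means = √(2/19) = 0.324 SD.
- P(|difference| > 0.5 SD) = P(|Z| > 0.5/0.324) = P(|Z| > 1.54) ≈ 0.12.
- With equal SDs at both times, the expected carry-over to follow-up is r times the baseline difference, where r is the baseline to follow-up correlation. A 0.5 SD imbalance carries over 0.5 × 0.5 = 0.25 SD at r = 0.5, and 0.05 SD at r = 0.1.

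**4. Precision gained from a baseline covariate.** Residual variance is multiplied by 1 − r², and the equivalent total sample is 38 / (1 − r²). The documents give no r, so a range is shown:

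| r (assumed) | 1 − r² | Variance reduction | Equivalent total N |
|---|---|---|---|
| 0.1 | 0.99 | 1% | 38.4 |
| 0.3 | 0.91 | 9% | 41.8 |
| 0.5 | 0.75 | 25% | 50.7 |
| 0.7 | 0.51 | 51% | 74.5 |

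**5. Covariate or change score?** A change score has variance 2(1 − r) relative to the postoperative value alone. Illustration with 17 per arm and a standardised difference of 0.96, where power without a baseline is 80%:

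| r (assumed) | Power, ANCOVA | Change-score variance factor | Power, change score |
|---|---|---|---|
| 0.1 | 80.4% | 1.8 | 55% |
| 0.3 | 83.6% | 1.4 | 66% |
| 0.5 | 89.9% | 1.0 | 80% |
| 0.7 | 97.5% | 0.6 | 95% |

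ANCOVA does not lose in this range. A change score loses power whenever r is below 0.5.

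**The case against.** The strongest reply is that nothing here threatens validity. A reader might infer that the comparison between arms is biased without a baseline. The documents do not support that: allocation is random, so postoperative values can be compared directly, and chance imbalance is already covered by the standard error and the 5% level. Nor does an imbalance pass in full into the result, as step 3 shows.

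A reader might also infer that no postoperative value can be related to the participant's own starting level. For local temperature that is too strong, because the unoperated side is a concurrent reference within the same person. It is only a partial one: it is itself postoperative, cannot show a participant's usual side-to-side difference, and may move with any systemic rise.

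For pain, the exclusions make a low starting level likely, and the sample size rests on a postoperative VAS level, so a postoperative comparison fits the plan. Recurrent infection is an accepted indication, so zero is not guaranteed, but the expected gain is small.

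It is also fair to say that the gain is slight if r is low, and that the unseen schedule figure might list these readings. All of this stands, and it limits the point to precision and description. It does not remove it: systemic temperature has no reference of any kind in the text. If the figure does schedule the readings, sections 3.1, 3.5 and 3.8 should say so.

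**Conclusion.** The point holds as a low-cost improvement in design, not as an error that invalidates the comparison. The readable text leaves systemic temperature, local temperature, VAS and NRS-101 without a preoperative value. The consequence is clearest for systemic temperature, partial for local temperature and probably small for pain. Chance imbalance of more than 0.5 SD has a probability of about 12% with all 38 participants, and it could be neither detected nor adjusted for. The precision forgone lies between 1% and 51% of residual variance for r from 0.1 to 0.7. That range is an assumption, since the documents give no correlation, and the conclusion also depends on the unseen schedule figure not adding these readings.

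**What to change.** Add to section 3.1 that the blinded evaluator who makes the postoperative measurements also records, before anaesthesia, systemic temperature and local temperature on both sides with the thermometer named in section 3.8. As a lower priority, add VAS and NRS-101 at the same contact. Amend sections 3.5 and 3.8, and the SPIRIT figure if needed, to match.

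State that the arms are compared on days 1, 2, 5 and 7 with the preoperative value as a covariate (ANCOVA or a mixed model), not as a subtracted change score. The reading precedes randomisation, so it is a valid covariate.

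The cost is an estimated two minutes per participant at an assessment that already takes place, using a touch-free thermometer and scales already in the study. No new visit or staff is needed. Participants operated on before the change would have no such reading.

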### Dysphagia

3.9

The evaluation of dysphagia will be performed through a numerical scale in which: (0) total absence of dysphagia; (1) dysphagia to solid foods; (2) dysphagia to any liquid or solid food. The patients will respond to the questioning on days 1, 2, 5, and 7 days after surgery.

### Evaluation of the presence and intensity of hematoma/bruise

3.10

The presence of hematoma/ecchymosis will be evaluated by measuring the largest diameter of colorimetric changes in the skin of the jugal and submandibular region at 1, 2, 5, and 7 days after surgery. The measure will be performed by the evaluator who will classify the occurrence of this result into 4 categories: none; larger diameter smaller than 4 cm; greater diameter between 4 and 10 cm, and larger diameter >10 cm.

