## Introduction

1

Photobiomodulation (PBM) is an emerging technique using red or near infrared light (low-power laser or light emitting diode [LED]) to modulate inflammation, accelerate wound healing, and reduce pain and discomfort in different clinical situations.^[1,2]^ The efficacy of PBM depends on the parameters, such as wavelength, power output, and energy. Different clinical situations require different PBM protocols. Most of the research on PBM in dentistry was carried out with low power/intensity lasers and some protocols are already well established using these lasers.^[2]^ However, few studies in dentistry were developed using LEDs, and most of them were performed to prevent/treat oral mucositis.^[3]^

Some studies have demonstrated a beneficial effect of LED (670 nm) on the incidence and severity of oral mucositis in participants undergoing oncological treatment.^[4–6]^ However, the near-infrared light in the 850 nm range has been shown to be capable of promoting vasodilation and the production of growth factors, as well as angiogenesis, leading to wound healing.^[7,8]^

In dentistry, one of the most common surgical procedures is the removal of retained third molars.^[2,9]^ This surgery generates great morbidity to the participants by causing pain, edema, and trismus due to surgical trauma.^[2,10,11]^ In recent years, several studies have shown beneficial effects of low intensity laser therapy in the postoperative period of lower third molar extractions.^[12–14]^. Despite the beneficial effects of LEDs on pain control and repair described in the literature, no studies were found to evaluate the effect of the use of LEDs in the postoperative period of third molar surgery. This is a relatively new technology and it is still under investigation especially in clinical trials.

The objective of the present study is to evaluate the efficacy of LED photobiomodulation in pain control, facial edema, trismus, temperature, dysphagia, hematomas, and quality of life after the extraction of retained lower third molars.

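### Bruise diameter is measured at each visit, but section 3.10 states the hematoma outcome only as four wide classes; recording and comparing the centimetres would keep information already collected

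*Protocol article*

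**What the plan says.** Section 3.10 (hematoma/bruise) assesses the outcome by "measuring the largest diameter of colorimetric changes in the skin" of the cheek and submandibular region on days 1, 2, 5 and 7. The evaluator then "will classify the occurrence of this result into 4 categories": none, under 4 cm, 4 to 10 cm, and over 10 cm. These classes are the only form in which the hematoma result is stated.

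Edema (3.6) and mouth opening (3.7) are also measured as distances, and no classes are applied to them.

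The Introduction lists the objective as efficacy in "pain control, facial edema, trismus, temperature, dysphagia, hematomas, and quality of life", so hematoma is a stated outcome. The Abstract's objective and the article's title leave it out.

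The Sample calculation (2.3) is "based on the pain analysis of the participants on the 3rd postoperative day evaluated by a visual analog scale (VAS) was performed". It states no power for hematoma. Statistical analysis (3.13) names no test for any outcome. It summarises quantitative variables by mean and standard deviation and qualitative ones by frequencies and percentages.

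**The concern.** The evaluator has a number in centimetres in hand and the protocol turns it into one of four classes. The second class holds every visible bruise under 4 cm, so bruises of 3.5 cm and 1.7 cm count as the same result. If only the class reaches the file, no later analysis plan can recover the centimetres. This is therefore a question about what is recorded, not only about which test is chosen.

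At stake is the power of one secondary comparison in a small trial. If LED mainly shrinks bruises without abolishing them, and most bruises are small, the classes would largely hide that effect.

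**Working it through.** **1. The plan's own figure.** Section 2.3 reports that "a minimum sample size of 17 cases per group was obtained, making a total of 34 participants for the study", at 80% power and 5% significance, for pain. It prints neither the difference nor the standard deviation, so 17 cannot be reproduced directly. Solving backwards (two-sided 5% assumed): d = (1.960 + 0.842) × √(2/17) = 0.96 by the normal approximation, or 0.99 by the noncentral t. The allowance for loss does reproduce: 17/0.90 = 18.9, rounded up to 19 per group, 2 × 19 = 38. None of this concerns hematoma.

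**2. Method.** Diameters were simulated under assumed distributions, and the Mann-Whitney test (two-sided 5%) was applied once to the diameter rounded to 0.1 cm and once to the four classes. Relative loss = 1 − power(classes)/power(cm). There were 2,000 to 6,000 runs per setting; at 2,000 runs the standard error is at most √(0.25/2000) = 0.011.

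For lognormal diameters with median m and log-SD σ, the share of visible bruises under 4 cm is Φ(ln(4/m)/σ). The tables average it over the two arms.

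**3. Everyone bruised, 17 per arm, LED halves the median, log-SD 0.7.**

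| Control median | Share under 4 cm | Power, cm | Power, classes | Relative loss |
|---|---|---|---|---|
| 12 cm | 0.17 | 0.773 | 0.698 | 10% |
| 6 cm | 0.47 | 0.750 | 0.664 | 11% |
| 4 cm | 0.67 | 0.753 | 0.552 | 27% |
| 3 cm | 0.79 | 0.774 | 0.455 | 41% |
| 2 cm | 0.91 | 0.770 | 0.208 | 73% |

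Example for the 3 cm row: control Φ(0.288/0.7) = 0.66, LED Φ(0.981/0.7) = 0.92, average 0.79; loss 1 − 0.455/0.774 = 41%.

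**4. Normal diameters, 17 per arm, d = 0.99.** Control mean 5, SD 2: 0.783 to 0.636 (19%). Mean 6, SD 3: 0.777 to 0.687 (12%). Mean 8, SD 3: 0.774 to 0.656 (15%). Mean 3, SD 2: 0.758 to 0.643 (15%). Mean 3, SD 1: 0.776 to 0.276 (64%). Mean 2, SD 0.7: 0.757 to 0.004 (almost all).

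**5. Some participants without a bruise, same share in both arms.**

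| Setting (control median, % with no bruise) | Share of visible under 4 cm | Power, cm | Power, classes | Relative loss |
|---|---|---|---|---|
| 19 per arm, log-SD 0.6: 5 cm, 10% | 0.57 | 0.74 | 0.58 | 22% |
| 5 cm, 20% | 0.57 | 0.52 | 0.37 | 29% |
| 3 cm, 20% | 0.82 | 0.52 | 0.18 | 65% |
| 2 cm, 10% | 0.93 | 0.73 | 0.11 | 85% |
| 17 per arm, log-SD 0.7: 6 cm, 30% | 0.47 | 0.236 | 0.179 | 24% |
| 3 cm, 30% | 0.79 | 0.244 | 0.099 | 59% |

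With no treatment effect (19 per arm, 3 cm, 20% with no bruise) the rejection rates were 4.55% on cm and 4.48% on classes, so the gain is not bought with false positives.

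**6. LED also raises the share with no bruise.** The classes keep this contrast, and the loss shrinks.

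- 17 per arm, 30% vs 50%: 6 cm, 0.491 to 0.446 (9%); 3 cm, 0.501 to 0.348 (31%); 2 cm, 0.498 to 0.288 (42%).
- 17 per arm, 50% vs 70%: 6 cm, 0.344 to 0.324 (6%); 2 cm, 0.336 to 0.230 (32%).
- 19 per arm, 20% vs 40%: 5 cm, 0.77 to 0.67 (13%); 3 cm, 0.77 to 0.52 (32%).
- 19 per arm, 2 cm: 10% vs 40%, 0.95 to 0.69 (27%); 10% vs 30%, 0.89 to 0.46 (48%).

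**7. Limit of the check.** Under the same rank test, the classes had less power than the centimetres in every setting. An unordered chi-square on the classes was usually weaker still (mean 6, SD 3: 0.435). It was not always weaker: with 30% unbruised in both arms and a 6 cm median it reached 0.306, above 0.236 for the rank test on cm, though a t-test on cm gave 0.336. Its type I error was not checked, and the protocol does not prescribe it.

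**The case against.** The strongest reply is that the document does not say the centimetres are lost. Section 3.4 puts the information from the evaluations into the evaluator's file, and section 3.13 describes every measured variable, with means and standard deviations for quantitative ones. A diameter is quantitative. Section 3.10 defines a grading, not a test, and the choice of variable and model may properly be left to an analysis plan that is not shown. This stands: a reader might infer that the protocol throws the measurement away, or prescribes an analysis of the classes, but the text settles neither. What remains is that the classes are the only stated form of the result, while edema and mouth opening stay as distances.

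A reader might also infer that the classes cost half or more of the power. The documents hold no figure on bruise size to support that. It arises under assumptions that put most bruises below 4 cm, chiefly with the same share of unbruised participants in both arms. An LED effect that shrinks bruises could also make some disappear, and the classes keep that contrast; section 3.10 is headed with presence as well as intensity.

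Nor do the documents support saying that the classes make a null result likely. With 20% unbruised in both arms, the rank test on the centimetres has only 52% power itself; with a 5 cm median and 10% unbruised, the classes still have 58%.

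Finally, the outcome is minor: it did not size the trial and no power is claimed for it.

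**Conclusion.** The point holds as a conditional one and is a low-cost improvement, not an error that threatens the trial. If the four classes are what is recorded and compared, section 3.10 loses information that the evaluator has already collected.

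Under the assumed distributions, with 17 to 19 per arm and a rank test:

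- The relative loss is roughly 6% to 30% when diameters spread over several classes or the unbruised share also differs between arms. At a 2 cm median it was 42% and 48% in two of the settings with a differing share.
- It is about 40% at a control median of 3 cm with everyone bruised.
- It is half or more only when most or nearly all bruises fall in one class (about 80% or more of visible bruises under 4 cm in the lognormal runs), or when power is already low.

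The bruise-size distribution, the unbruised share and the treatment effect are all assumed, so the range should be quoted and not a single figure. The sample size of 38 and the pain comparison are unaffected.

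**What to change.** In section 3.10, state that the evaluator records the largest diameter in cm, with 0 when there is no bruise, in the evaluator's file at days 1, 2, 5 and 7. State that the arms are compared on that value with one prespecified rank-based or ordinal method covering the four visits, and that the four classes are used for description only.

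The cost is one field on the form and one sentence of analysis wording; the measurement is already being made. If the centimetres are already kept, only the sentence is needed.
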